## Abstract

**Background:**

Fatigue is rated as the most distressing side effect of radiotherapy treatment for curable breast cancer. About four in ten women treated experience fatigue, which can last for years after treatment. The impact of this debilitating tiredness is loss of independence and impaired physical and mental function. Our study will take a behavioural intervention with demonstrated effect in treating fatigue in a mixed group of chemotherapy patients and adapt it for women undergoing radiotherapy for early breast cancer. The purpose of this trial is to evaluate the feasibility of delivering the intervention in the radiotherapy pathway for patients at a high risk of fatigue and to explore participants’ experiences of the trial and intervention.

**Methods:**

A pragmatic single-site non-blinded feasibility trial of a behavioural intervention. Main inclusion criteria are prescription of the UK standard 40 Gy in 15 fractions over 3 weeks of radiotherapy (± tumour bed boost) for early (stage 0–IIIa) breast cancer. The total projected sample size after attrition is 70. A previously developed fatigue risk score tool will be used to predict individual’s likelihood of experiencing fatigue. Thirty women predicted to be at a high risk of experiencing significant fatigue will be allocated in the ratio 2:1 to the behavioural intervention or education trial arms, respectively. These feasibility trial participants will be assessed at baseline, after 10 and 15 fractions of radiotherapy and 10 days, 3 weeks and 6 months after radiotherapy. A further 40 women predicted to be at a lower risk of fatigue will join a risk score validation group.

Measures to assess feasibility include recruitment, retention and completion rates and variation in implementation of the intervention. Process evaluation with intervention providers and users includes fidelity and adherence checks and qualitative interviews to understand how changes in behaviour are initiated and sustained.

**Discussion:**

This feasibility study collates data to both inform the progression to and design of a future definitive trial and to refine the intervention.

**Trial registration:**

ISRCTN 10303368. Registered August 2017 (retrospectively registered); Health and Care Research Wales Clinical Research Portfolio (CRP) registration 31419.

## Background

Breast cancer is the most common UK female malignancy with 55,000 cases diagnosed annually [1]. Two thirds of these women will undergo breast conserving surgery followed by adjuvant radiotherapy to prevent loco-regional recurrence. Selective prescription of systemic anti-cancer therapies also contributes to a 5-year survival of 87% for breast cancer [2]. Health policy expects that all survivors of cancer get the support they need to lead active lives [3] and focusses on ‘interventions to help people cope with the side-effects of treatment’ [4]*.*

Patients with early breast cancer rate fatigue as the most distressing side effect of treatment and it is the predominant mediator of wellbeing in this population [5]. Radiotherapy-related fatigue (RRF) disrupts daily functioning—the ability to return to work, to undertake family responsibilities and to maintain social lives [6]—for women who are often of working age (average age of diagnosis is 57 years) [7]. Four in ten women receiving radical radiotherapy experience clinically significant fatigue [8, 9], which can last for months, or years, after treatment [10]. This chronic fatigue is strongly associated with the severity at the end of adjuvant treatment [11].

Whilst results are mixed and pooled effect sizes small to moderate, high-level review evidence reports psycho-educational approaches have demonstrated effectiveness on fatigue reduction (pooled mean effect size − 0.31; range − 0.43 to 1.10, 95%CI − 0.38 to − 0.25) [12]. Effective fatigue interventions are brief, delivered individually to specific disease and treatment groups and based on need [13]. Participants in successful interventions were broadly educated about fatigue, learnt to balance activities and rest, were provided with emotional support and learnt self-management techniques [10]. Cognitive behavioural therapy (CBT)-orientated interventions have shown promise (mean effect size 0.47) [12] in treating fatigue in chronic fatigue syndrome, breast cancer survivors and chemotherapy populations [14]. Goal setting, self-monitoring and feedback are likely to be key techniques for encouraging individual behaviour change [15]. Motivational interviewing (MI) techniques show how a counsellor can use an individual’s concerns and needs as a basis for movement towards a goal [16]. Furthermore, an evidence synthesis by the National Cancer Survivorship Initiative (NCSI) highlights self-efficacy as a key component of effective self-management interventions [17]. The use of physiological feedback, for example a physical activity monitor, can be a powerful tool to promote self-efficacy [18, 19]. The NCSI work also identifies that information alone ‘can increase knowledge and prepare patients for change, and should be provided for all survivors’, but ‘additional tailored support from healthcare professionals’ will be needed for some [17]. Identifying patients who require additional support remains a challenge, but evidence suggests they may be experiencing fatigue and/or anxiety, lacking in a supportive network or have a diagnosis other than invasive ductal carcinoma [20].

The value of education alone, relative to any additional benefit from supportive guidance/contact with a health professional, is unclear when treating cancer-related fatigue. The current intervention has been designed to be consistent with the aspiration of a standardised intervention that is deliverable in a future trial by a range of trained health professionals compared to a fully flexible intervention that may rely on the skills of a professional counsellor: the two interventionists in the current study both have experience of counselling theory and practice. Most cancer-related fatigue studies have been carried out with patients who have developed long-term problems, often from heterogeneous patient groups*.* The aim of the current work is to prevent long-term problems arising within a homogenous population. Of the research conducted around treatment, most involves patients receiving chemotherapy rather than radiotherapy*.* This feasibility study seeks to clarify the preceding uncertainties by testing a psycho-educational behavioural intervention, delivered early in the radiotherapy pathway, to help patients with stage 0–IIIa disease self-manage fatigue.

The *primary aim* of our feasibility study is to evaluate trial processes to determine if the design is feasible and acceptable to deliver in the radiotherapy pathway. The *secondary aim* is to evaluate a participant’s experiences and opinions of the intervention, as a basis for refinement for a definitive trial.

## Methods

### Study design

A pragmatic parallel-group, randomised feasibility trial (ISRCTN 10303368). Participants will be screened for fatigue risk and dichotomised into low/high risk groups. The higher risk group will comprise the feasibility trial participants, who will be randomly allocated to ‘behavioural intervention’ or ‘education alone’ groups, in the ratio 2:1. Participants at a lower risk of fatigue will join a fatigue risk score validation group: this validation work is required before use in a prospective definitive study. A schema of participant pathways for both groups is shown in Fig. 1.

**Fig. 1 Fig1:**
[figure not shown]
Study schema

### Study setting and participant selection

This single-site study will be conducted at a regional cancer centre (referred to as ‘the cancer centre’), which provides non-surgical specialist cancer services to a diverse population of 1.5 million in south east Wales.

### Patient identification

The radiotherapy planning clinical team will screen consecutive patients for initial approach based on the eligibility criteria outlined below. For patients who have not been prescribed adjuvant chemotherapy, screening will be done when the planning lists are compiled using the cancer centre’s electronic patient records system. For patients receiving adjuvant chemotherapy prior to radiotherapy, their medical notes will be screened at their point of consent for radiotherapy (typically chemotherapy cycle four or five of six).

### Inclusion and exclusion criteria

Patients meeting any of the following criteria may be included in the study:Females > 16 years;Diagnosis of stage 0–IIIA breast carcinoma;Standard 4000 cGy in 15 fractions over 3 weeks ± nodal irradiation ± tumour bed boost;Able to complete outcome measures.

Patients will be eligible if they have received prior chemotherapy or are receiving monoclonal antibodies or endocrine treatment as maintenance therapy.

If any of the following criteria apply, patients cannot be included in the study:Not prescribed radical radiotherapy;Concurrent chemotherapy;Serious comorbidity causing chronic fatigue;Psychiatric illness requiring secondary care intervention;Too ill to engage with the intervention in the opinion of the clinical care team.

### Recruitment process

Patients’ usual care involves visiting the cancer centre for a scan from which their radiotherapy treatment is planned. Timings vary, but this typically happens 3 weeks before starting treatment. After their planning scan, a clinical member of the planning team will briefly outline the study to patients. Eligible and willing patients will be introduced to the researcher (SG or NC) and have the opportunity to discuss the study. People who are interested in the study will be given an invitation pack containing a letter of invitation, patient information leaflet, model consent form and a prepaid reply slip (labelled with an anonymised study number.) If a researcher is not available, then a briefed pre-treatment radiographer can give the patient a study pack. Patients can indicate their interest by posting the reply slip (within 5 days) or by choosing on the day to receive a telephone call within 7 days. All patients expressing interest in participating in the study, via face-to-face invitation or the reply slip, will be contacted by telephone to discuss the study. All patients will be given a minimum of 24 h after the initial invitation before being phoned and will have the opportunity to have any questions answered. Study eligibility will be checked and fatigue risk status measured in patients who express a wish to participate.

### Fatigue risk status

Participant risk status will be screened using the Fatigue Risk (Propensity) Score (Fatigue Propensity Score = [3 + (0.13 × fatigue) + (0.16 × anxiety) + 1.1 if diagnosis is not invasive ductal cancer]) [20]. We previously developed this tool to generate a fatigue risk percentage based on pre-treatment factors, as a means to identify patients who are experiencing clinically significant fatigue or are at higher risk of developing fatigue during radiotherapy. The score was generated from study data evaluating variables that contribute to RRF [9]. This data was drawn from 100 women undergoing radiotherapy for breast cancer, none of whom had received prior chemotherapy. Performance of the tool will therefore be evaluated in women who have and have not received chemotherapy. The risk score is weighted towards fatigue level, but the other two items independently add predictive ability. A score of between 3 and 15 is generated. A threshold for high risk can then be applied, which represents a trade-off between sensitivity and specificity, in accordance with clinical judgement or resource constraints [20]. It is anticipated that approximately 50% of patients will score ≥ 5, a threshold that has demonstrated good prediction of patients as fatigued or not fatigued.Scoring ≥ 5 will initiate randomisation to one of the feasibility trial arms.Participants scoring ≥ 5, who decline entry into the feasibility trial will be offered the opportunity to enter the ‘fatigue risk score validation group’.Patients scoring < 5 will join the ‘fatigue risk score validation group’. Participants in this group will be sent a pack containing a consent form and two fatigue questionnaires to be completed at the end of their radiotherapy treatment.

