### Informed consent

The researcher will arrange a mutually convenient date and venue for patients to give consent for the trial. This should typically happen within 10 days of invitation, to enable participants to be allocated to the respective group with sufficient time before their start of radiotherapy. The patient’s written consent will be obtained using the study consent form. Baseline measures will then be completed and the allocation decided via a central randomisation service. The researcher will explain and leave the appropriate study pack with the participant.

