### Fatigue risk score validation group

Participants who are predicted to be at a low risk of fatigue will be allocated to a validation group. These women will fill in a Functional Assessment of Chronic Illness Therapy (FACIT-F) Fatigue Scale [24] on the last day of their treatment and at 10 days and 6 months after their radiotherapy finishes. Any patients estimated to be at a higher risk of fatigue who have declined entry into the feasibility trial will be offered the opportunity to enter the validation group. The fatigue data from the trial control arm participants will also be included. The group data will be correlated to the fatigue risk score calculated before treatment and thereby enable an assessment of the accuracy of the prediction tool. Analysis will be stratified by prior chemotherapy/no chemotherapy. The predictive ability of the tool will be evaluated with a view to potential use in selecting participants in an effectiveness trial.

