### Study assessments

#### At screening

The patient’s cancer diagnosis and reasons for ineligibility will be recorded. A screening log will be maintained that records the numbers of people who:Are eligible/ineligible;Are approached;Decline to be contacted and reasons for declining (if proffered);Score above and below the fatigue score threshold;Decline at the point of consent or trial group allocation.

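### Validation-group consent travels with the end-of-radiotherapy questionnaires and need not be returned before the outcome is known, so entry to the accuracy sample may depend on returning the outcome

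*Protocol article*

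**What the plan says.** The protocol article places the steps as follows.

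- **Scoring.** Recruitment process: interested patients "will be contacted by telephone to discuss the study", and "Study eligibility will be checked and fatigue risk status measured in patients who express a wish to participate". The risk score therefore comes before the written-consent step.
- **Trial consent.** Informed consent: "The researcher will arrange a mutually convenient date and venue for patients to give consent for the trial". Written consent is followed by baseline measures and randomisation, with time left before radiotherapy.
- **Validation consent.** Fatigue risk status: women scoring below 5, and women scoring 5 or more who decline the trial and accept the alternative, form the validation group. They are sent "a pack containing a consent form and two fatigue questionnaires to be completed at the end of their radiotherapy treatment". No consent visit and no earlier return date for the form is described for them.
- **Analysis.** Fatigue risk score validation group: FACIT-F is scheduled on the last treatment day, at 10 days and at 6 months. Control-arm fatigue data are added. "The group data will be correlated to the fatigue risk score calculated before treatment", with stratification by prior chemotherapy.
- **Log.** At screening: the log counts, among others, patients who "Score above and below the fatigue score threshold" and those who decline at consent or allocation.

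**The concern.** Study design says the validation is needed before the score can be used in a definitive study. The result therefore matters, although it is ancillary to the primary feasibility aim.

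A prediction tool should be judged in people enrolled before their outcome is known. Here controls are enrolled that way, while women in the validation group may in effect enrol when they post back the outcome. If return is related to fatigue, the sample is selected on the very quantity the score is meant to predict, and one accuracy analysis mixes two entry rules. With about 40 validation women and 10 controls, split again by prior chemotherapy, a few selectively absent women could change the estimate.

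There is also a denominator problem. A woman who sends nothing back may have refused, or may have agreed and been lost, and the described procedure does not distinguish the two.

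**Working it through.** **1. The plan's own figures.** Sample size gives final groups of 20, 10 and 40, 10% loss, and about 77 to recruit.
- 20 + 10 + 40 = 70. 70/0.9 = 77.8, so 78; 70 × 1.1 = 77; 77 × 0.9 = 69.3. The stated 77 reproduces as an approximate figure.
- Validation group alone: 40/0.9 = 44.4, so 45 to recruit.

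**2. The two entry routes into one analysis.**

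| | Trial controls | Validation women |
|---|---|---|
| Risk score | before consent | before consent |
| Consent | before baseline and radiotherapy | form in the outcome pack; return date not fixed |
| Denominator before the outcome | yes | not fixed |

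Evaluation of the feasibility of the trial defines retention over those with baseline outcome measures. None are scheduled for the validation group, so that rate does not cover it.

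**3. What 10% loss can mean here.** If consent arrives only with the first questionnaire, packs needed for 40 women = 40/(return rate). The return rate is an assumption, as the article gives none.
- 90%: 45 packs; 80%: 50; 70%: 58; 50%: 80.

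Only the 90% case matches the planned loss, and the shortfall in the others could be refusal or loss. Attrition after the first returned form would still be visible at the later assessments.

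**4. Possible size of selection.** Let p be the true fatigue rate in low-score women, and r and s the return rates of fatigued and non-fatigued women. Observed rate = pr/(pr + (1 − p)s). All inputs are assumed; p = 0.20.

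| r | s | Calculation | Observed rate |
|---|---|---|---|
| 0.8 | 0.9 | 0.16/0.88 | 18.2% |
| 0.6 | 0.9 | 0.12/0.84 | 14.3% |
| 0.5 | 0.9 | 0.10/0.82 | 12.2% |
| 0.9 | 0.7 | 0.18/0.74 | 24.3% |

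In the third row half of the tool's misses go unreturned (1 − 0.5), while the observed rate falls by (0.20 − 0.122)/0.20 = 39%. These are different quantities. In the last row fatigued women return more often, and the error reverses.

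**5. Direction for sensitivity.** Let a, b and c be the numbers of fatigued women among controls, high-score decliners and low-score women, with return rates k, h and l. True sensitivity is (a + b)/(a + b + c); the observed value is (ka + hb)/(ka + hb + lc). The observed value is too high if l is below (ka + hb)/(a + b) and too low if l is above it. The article gives none of these rates.

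**The case against.** The strongest reply is that the sentence does not say when consent is returned. Completion at the end of radiotherapy may apply only to the questionnaires. The article treats women scoring below 5 as joining the group outright, and it applies 10% loss to a recruited total, which suggests enrolment before follow-up. Return instructions are also a detail that an article may leave to the full protocol. This stands to the extent that dependence on the outcome is a possibility and not a stated rule. It does not remove the point: the article describes a specific procedure, and that procedure allows consent and outcome to arrive together.

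Four stronger readings might be inferred, and the document does not support them.

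- *Non-returners leave no trace.* The screening log counts women above and below the threshold and those declining at consent. For women below 5, non-returners follow by subtracting forms received. What is missing is any provision to compare their individual scores with those of returners.
- *Selection acts only on low scores.* Women scoring 5 or more who decline the trial receive the same pack.
- *Accuracy is overstated.* No passage says that fatigued women return less often, and fatigued high-score decliners who stay silent would be lost hits, which pushes apparent sensitivity down.
- *Earlier consent cures the bias.* If a consented woman does not return FACIT-F, her outcome is still missing, and complete-case rates would be those in the table above.

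**Conclusion.** The point holds in a limited form. As written, the validation group's consent can arrive with the outcome used to judge the score, whereas controls in the same analysis consent beforehand. Entry may therefore depend on returning the outcome; refusal and loss merge at the first assessment; and returners and non-returners cannot be compared by score, although non-returners can be counted. The last statement assumes that individual scores of women who never consent are unavailable for analysis; the article describes the log only as counts.

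The size is not known. Under the assumed inputs, a true 20% fatigue rate in low-score women could appear as anything from 12.2% to 24.3%, so neither the amount nor the direction of bias is established. The matter should be corrected because the validation is meant to support selection for a later trial. It does not undermine the primary feasibility aim.

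A related inconsistency needs settling: the pack holds two questionnaires for the end of radiotherapy, while the validation section lists three assessment times.

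**What to change.** 1. Send the validation consent form straight after risk scoring and ask for it back before the first fraction. Have it cover use of the pre-treatment risk score.
2. Define the validation denominator as women consented before treatment.
3. Report FACIT-F non-return among them by risk score and prior chemotherapy, and add a sensitivity analysis for non-return. Report from the screening log how many scored women did not consent.
4. Reconcile the two questionnaires under Fatigue risk status with the three times under Fatigue risk score validation group.

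The timing is workable. Planning is typically 3 weeks before treatment, and trial consent is typically within 10 days of invitation. The same target here leaves about 21 − 10 = 11 days.

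The cost is one earlier mailing step, a sentence in the consent form and a minor amendment. A few women may not return the form in time and would be lost to the validation. Missing outcomes will remain, but selective non-return becomes measurable and refusal can be separated from loss.

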### Sample size

We aim to recruit approximately 77 participants across all study groups. Assuming a 10% loss to follow-up, this will yield final sample sizes of 20, in the intervention group, and approximately 10 and 40 in the control and fatigue risk score validation groups, respectively. These figures are based on logistical grounds and are informed by previous experience in this setting. Assuming a 50% recruitment rate, we would need to approach about 160 eligible women across the 12-month study duration to achieve our planned sample. Recruitment will close when 20 participants have been recruited to the intervention arm.

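### Recruitment closes at 20 recruited to the intervention arm, but 20 is also that arm's stated size after 10% attrition; as written, about 18 intervention and 9 control participants remain

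*Protocol article*

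**What the plan says.** The Sample size section sets the overall target: "We aim to recruit approximately 77 participants across all study groups". It then converts that target to numbers after attrition: "Assuming a 10% loss to follow-up, this will yield final sample sizes of 20, in the intervention group", with "approximately 10 and 40 in the control and fatigue risk score validation groups, respectively". The abstract's Methods paragraph confirms that these are retained numbers: "The total projected sample size after attrition is 70".

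The last sentence of the Sample size section gives the stopping rule: "Recruitment will close when 20 participants have been recruited to the intervention arm".

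Three other places bear on this:

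- The abstract has thirty high-risk women allocated 2:1 and a further 40 lower-risk women joining the validation group.
- Fatigue risk status states "It is anticipated that approximately 50% of patients will score" at or above the threshold of 5. It lets women above the threshold who decline the trial enter the validation group instead.
- Evaluation of the feasibility of the trial counts recruitment by consent and defines retention separately.

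**The concern.** The intervention arm's 20 appears once as what is left after 10% loss and once as the count at which recruitment stops. If 10% are lost, a trial that stops at 20 recruited does not finish with 20. The control arm is tied to the intervention arm by the 2:1 ratio, so it falls short in step.

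The abstract makes the same slip. Thirty allocated plus a further 40 is 70 women entering, yet the same paragraph gives 70 as the total after attrition.

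The stopping rule is an operational instruction, so staff who follow it will end with fewer women than the section promises. What is at stake is the number of women with follow-up data from whom the parameters of the definitive trial are to be estimated, and the number available to validate the risk score. The validation group is also exposed because nothing but the intervention arm's count decides when its recruitment ends.

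**Working it through.** **Inputs.** Target about 77; loss 10%; final sizes 20, about 10 and about 40; closure at 20 recruited to intervention (all from Sample size). Total of 70 after attrition (abstract). Allocation 2:1 (Group allocation). About 50% scoring 5 or more, and the route for decliners (Fatigue risk status).

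**1. The plan's own figure.** 20 + 10 + 40 = 70. Inflating for 10% loss gives 70 / 0.9 = 77.8, or 70 x 1.10 = 77 by the simpler method. In the other direction, 77 x 0.9 = 69.3. The stated 77 is reproduced, and it makes sense only if 20, 10 and 40 are retained numbers. By group, the recruits needed are:

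| Group | Stated final size | Recruits needed (size / 0.9) |
|---|---|---|
| Intervention | 20 | 22.2 |
| Control | 10 | 11.1 |
| Validation | 40 | 44.4 |

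The rounded split 22 + 11 + 44 = 77 matches the target. The number to be approached also agrees: 77 / 0.5 = 154, against about 160 stated.

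**2. The closure rule as written.** Intervention: 20 x 0.9 = 18. Control: 20 / 2 = 10 recruited, and 10 x 0.9 = 9. If losses are independent at 10%, the chance that all 20 are retained is 0.9^20 = 12%. The chance of retaining at least 20 is 62% with 22 recruited and 81% with 23.

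**3. Total with the validation group at its full 44.** Recruited: 20 + 10 + 44 = 74. Retained: 74 x 0.9 = 66.6, about 67 against 70.

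**4. Validation group when recruitment closes.** At closure 30 women have been randomised. Let d be the number of high-risk decliners who join the validation group. Assume that half of all women score 5 or more, that every lower-risk woman joins, and that every high-risk decliner joins. Then there are 30 + d high-risk and 30 + d lower-risk women, and the validation group is (30 + d) + d = 30 + 2d.

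| d | Validation recruited | Validation retained (x 0.9) | Total retained, with 18 + 9 |
|---|---|---|---|
| 0 | 30 | 27 | 54 |
| 7 | 44 | 39.6 | 66.6 |

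At d = 7, the decliners are 7 of 37 high-risk women, or 19%. A total of 77 recruited requires 60 + 2d = 77, so d = 8.5. The documents give no value for d.

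**5. Effect on precision.** Among retained intervention participants, the standard error of a mean grows by a factor of sqrt(20 / 18) = 1.05. For a rate of 70% among those randomised, the Wald 95% half-width is 1.96 x sqrt(0.21 / 30) = 16.4 percentage points with 30 women and 1.96 x sqrt(0.21 / 33) = 15.6 with 33.

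**The case against.** The strongest reply is that the discrepancy is small and the section does not claim exactness. The figures rest on logistical grounds, 77, 10 and 40 are all given as approximate, and the article says that the trial is not powered for effectiveness. This stands as a statement about size: the certain shortfall is two intervention women and one control, with no consequence for power or error rates. It does not remove the contradiction. The intervention arm's 20 and the abstract's 70 carry no such qualifier, recruitment and retention are defined separately, and nothing in the article replaces women who are lost.

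Two stronger readings are tempting, and the documents do not support them.

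- A reader might infer from the 50% figure that the study will retain only 54 women, 23% fewer than 70, with 27 in the validation group. That needs exactly half at high risk and no decliners entering validation. The article provides for such decliners, and seven of them bring the group to 44. The control arm's fatigue data are also to be used in the validation. So a validation shortfall is possible but not established.
- A reader might infer that these final sizes set the precision of every feasibility rate. They do not. The stated denominators are women on clinic lists for eligibility, eligible patients approached for recruitment, and women with baseline measures for retention. For the last of these the trial contrast is about 30 against 33 women, less than one percentage point in the half-width computed above.

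**Conclusion.** The point holds for the two randomised arms. Under the closure rule and the plan's own 10% loss, the expected final sizes are about 18 and 9, not 20 and about 10. This rests only on the stated loss rate and the 2:1 ratio. The inflation from 70 to 77 is sound; the closure rule is what disagrees with it, and the abstract repeats the confusion.

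For the validation group the fault is narrower. Its size at closure is left undetermined because it has no closing count. A total near 70 could still be reached if enough high-risk decliners joined it, but the intervention arm would still end at about 18. The consequence is a modest loss of precision and a stated size that the design does not deliver.

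**What to change.** The simplest change keeps the closure rule and restates the numbers: 20 and about 10 randomised, about 18 and 9 expected after 10% loss. Give the validation size as a range, with the assumed high-risk share and number of decliners written beside it, for example 30 recruited if none join and 44 if seven do. Bring the overall target and the abstract into line, so that the numbers entering and the numbers after attrition are labelled as such.

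Alternatively, if 20 retained is the intention, set the trigger at 22 to 23 recruited to the intervention arm, which is consistent with the stated 77, and correct the abstract's thirty allocated to about 33. Under this option, give the validation group its own closing count if about 40 retained is a firm aim.

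The first option costs only wording, and the stated sizes become slightly less favourable. The second costs two or three more intervention participants and one or two more controls, which the target of 77 already allows for.

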### Group allocation

The nature of the intervention means it will not be possible to blind either the researcher or participants to their arm allocation. Analysis of outcome measures will be conducted blind to participant allocation where possible. Randomised group allocation and retention of randomisation codes will be via a central online database service [www.sealedenvelope.com] [21]. This remote allocation service removes the possibility of the researcher influencing group allocation. Allocation to the behavioural intervention arm will be in the ratio 2:1 using a permuted block protocol. A stratification variable will be age (< 57 years and ≥ 57 years). The researcher will inform the psychology team delivering the intervention of patients allocated to the intervention arm as soon as practically possible via a standard referral form. These participants will then be discussed at a psychology team meeting before allocation to one of the two interventionists.

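### The figure of 20 for the intervention arm is both its size after 10% loss and the recruited number at which recruitment closes, so about 18 and 9 women, not 20 and 10, are expected at follow-up

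*Protocol article*

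**What the plan says.** Three statements in the Sample size section of the protocol article bear on this.

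- Recruitment target: "We aim to recruit approximately 77 participants across all study groups".
- Result after loss: "Assuming a 10% loss to follow-up, this will yield final sample sizes of 20, in the intervention group", with "approximately 10 and 40 in the control and fatigue risk score validation groups, respectively".
- Closing rule: "Recruitment will close when 20 participants have been recruited to the intervention arm".

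The same section gives the basis for the sizes: "These figures are based on logistical grounds and are informed by previous experience in this setting". It also assumes a 50% recruitment rate and an approach to about 160 eligible women.

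The abstract (Methods) says "The total projected sample size after attrition is 70" and then "Thirty women predicted to be at a high risk of experiencing significant fatigue will be allocated in the ratio 2:1". Group allocation confirms the ratio: "Allocation to the behavioural intervention arm will be in the ratio 2:1 using a permuted block protocol".

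**The concern.** One number stands for two different quantities. As a final size, 20 is what remains after the loss allowance. As a closing rule, 20 is a count of women entered, before any loss. If recruitment stops at 20 entered, the intervention arm's share of the allowance is never recruited, and with 2:1 allocation neither is the control arm's share. The abstract repeats this, because the 70 after attrition is made up of 30 + 40 and the 30 is also the number allocated.

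Two things are at stake. The article states final arm sizes that its own rule is not expected to deliver. Staff running the trial also cannot tell whether to stop at 20 or at about 22 women in the intervention arm.

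**Working it through.** **Inputs.** From Sample size: about 77 recruited; 10% loss; final sizes of 20, about 10 and about 40; closure at 20 recruited to the intervention arm; 50% recruitment rate. From the abstract: 70 after attrition and 30 allocated. From Group allocation: ratio 2:1.

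**Step 1: reproduce the plan's 77.** The final sizes sum to 20 + 10 + 40 = 70. Inflating for 10% loss gives 70 / 0.9 = 77.8, or 70 × 1.1 = 77 by the simpler method. Going forward, 77 × 0.9 = 69.3. All of these agree with a stated approximate 77, so that figure is reproduced.

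**Step 2: see what 77 implies by group.** Applying the same inflation to each group:

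| Group | Final size | ÷ 0.9 | × 1.1 |
|---|---|---|---|
| Intervention | 20 | 22.2 | 22 |
| Control | 10 | 11.1 | 11 |
| Validation | 40 | 44.4 | 44 |
| Total | 70 | 77.8 | 77 |

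With loss spread evenly, the 77 therefore contains about 22 intervention and 11 control women, 33 randomised in all.

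**Step 3: apply the closing rule.** Recruitment stops at 20 intervention women, which at 2:1 means about 10 controls and about 30 randomised. After 10% loss:

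- intervention: 20 × 0.9 = 18
- control: 10 × 0.9 = 9
- total: 27, against 30 stated, a shortfall of 3/30 = 10%

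**Step 4: look for text that would reconcile the two.** Nothing in the article replaces women who are lost, and nothing defines recruited as retained. If each woman independently had a 10% chance of loss (an assumption), all 20 would be retained with probability 0.9^20 = 12%.

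**Step 5: carry the closing rule through to the totals.** If validation recruitment stays at about 44, the total recruited is 30 + 44 = 74, and 74 × 0.9 = 66.6, about 67, remain. At a 50% recruitment rate, 74 / 0.5 = 148 women would be approached, against 77 / 0.5 = 154 for the stated target and about 160 in the text.

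**The case against.** **The 10% is stated for the whole sample, not for each arm.** Literally, the figures could all hold if no randomised woman were lost. With 30 randomised, 77 − 30 = 47 would enter the validation group and all 77 − 70 = 7 losses would fall there, a loss of 7/47 = 15%. Nothing in the article says this and it is implausible. So it is too strong to say that the statements are logically incompatible, but the inconsistency is not removed.

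**The study is an unpowered feasibility trial, and the gap is two women in one arm and one in the other.** This stands, and it limits the importance of the point. The sizes rest on logistics, so no power or precision target is missed.

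**A reader might infer that everything estimated for the definitive trial rests on fewer women than stated.** The article does not support that. Under Evaluation of the feasibility of the trial, eligibility is a proportion of women on clinic lists, recruitment is consents over eligible women approached, retention is divided by women with baseline measures, and adherence counts sessions. None has a post-loss denominator.

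**A reader might also go further on three details.**

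- That 77 is itself miscalculated. It is not: 69.3 fits an approximate 77 and 70.
- That the comparison of arms loses precision. Data analysis plans only to describe changes over time by group and disclaims a formal analysis of the primary outcome, so an interval for an arm difference is not a planned result.
- That closing on one arm's count leaves the control number to chance. The control size is already given as approximate, and the block size needed to quantify its variation is not given.

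**Conclusion.** The point holds in a limited form. The Sample size section uses 20 both before and after loss, and the abstract does the same with 30. Under the closing rule and a 10% loss that applies equally to both arms, about 18 intervention and 9 control women are expected at follow-up, 27 rather than 30. The 9 is approximate, because blocked allocation within age strata can leave the control count slightly off 10 at closure.

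The consequence is confined to the follow-up scale outcomes described by group, including FACIT-F at 10 days after radiotherapy, which rest on slightly fewer women than stated. The feasibility rates that serve the primary aim are not affected. This is a modest inconsistency that is cheap to correct.

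**What to change.** Choose one of two repairs and make it in both the Sample size section and the abstract.

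1. **Keep the closing rule and restate the sizes.** Give 30 randomised (20 + about 10) and about 18 + 9 after 10% loss. If validation recruitment stays at about 44, change the total recruited from 77 to about 74 and the total after attrition from 70 to about 67. Recheck the 160 to be approached, since 74 / 0.5 = 148.
2. **Keep 77 and 70 and change the closing rule.** State closure on the inflated number: about 22 recruited to the intervention arm, 33 randomised in total. This fits within the plan's own target (33 + 44 = 77) and gives 33 × 0.9 = 29.7, about 30, after loss. In the abstract, the number allocated becomes about 33, with 30 as the number remaining.

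Either costs a few edited sentences. The first makes the stated sizes slightly less favourable. The second means randomising about three more women than the present closing rule would, but adds none to the planned total.
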